### Recruitment

Following the randomization of the clusters, lists of pregnant women in the randomized kebeles were obtained from the health extension worker’s registration book. Midwives then identified eligible pregnant women using 2 strategies: the last menstruation period (LMP) and the fundal height measurement technique (in the case of an unknown LMP) to determine the GA of mothers. The data collector provided a detailed explanation of the inclusion criteria and overall intervention procedure to eligible mothers by using the information sheet. Eligible pregnant mothers were enrolled in the intervention after obtaining informed consent regarding their willingness to give their phone number for the intervention and their approval to receive text messages to their own or their family’s phone during the intervention period. The recruitment was done after randomly selecting 28 participants from a list of eligible pregnant mothers in each cluster. After recruitment, information, such as the participant’s name, mobile phone number, and GA, was gathered during the baseline assessment. This information was then entered into the software to dispatch the messages according to the GA of those assigned to the intervention arm.

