### Randomization, Allocation Concealment, and Blinding

A total of 6 primary health care units, 2 from each district, were randomly selected, and kebeles in these primary health care units were used as units of randomization for the trial. A simple randomization with a 1:1 allocation was used to randomize the clusters (kebeles). After listing 30 kebeles that fulfilled the eligibility criteria, 21 of them were randomly selected for randomization. To assign the clusters to the intervention groups (gain-framed group, loss-framed group, and control group), the following steps were followed. First, the 21 clusters were alphabetically listed and labeled 1 to 21. Next, random numbers were generated using Excel 2019 (Microsoft Corp), and the generated values were copied and pasted as values next to the list of clusters. The list was then sorted in ascending order based on the generated random number. Finally, the first 7 clusters in the sorted list were assigned to the gain-framed group, the next 7 to the loss-framed group, and the last 7 to the control group. After the randomization, eligible pregnant women with a GA of 16-20 weeks were identified from the selected cluster by midwives. The midwives used 2 strategies: the LMP and the fundal height measurement technique in the case of an unknown LMP to determine the GA of mothers (Multimedia Appendix 2).

The allocation process was done by a person who was not involved in the implementation of the trial, and it was masked from the researcher involved in the implementation of the intervention. The interviewers who collected the data were blind to the intervention assignment. It is not possible to blind participants due to the nature of the intervention.

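### Women were listed, screened, dated and enrolled after their kebele had been allocated, and the staff who judged eligibility are not among those stated to be masked

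*Protocol article*

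**What the plan says.** Two sections of the protocol article give the same order. Recruitment: "Following the randomization of the clusters, lists of pregnant women in the randomized kebeles were obtained". Randomization, Allocation Concealment, and Blinding: "After the randomization, eligible pregnant women with a GA of 16-20 weeks were identified from the selected cluster by midwives".

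The later steps are in Recruitment:
- **Eligibility and dating.** "Midwives then identified eligible pregnant women using 2 strategies: the last menstruation period (LMP) and the fundal height measurement technique". Fundal height is the fallback when the LMP is unknown.
- **Draw.** "The recruitment was done after randomly selecting 28 participants from a list of eligible pregnant mothers in each cluster".
- **Consent.** "Eligible pregnant mothers were enrolled in the intervention after obtaining informed consent regarding their willingness to give their phone number". It also covers "their approval to receive text messages to their own or their family’s phone during the intervention period".
- **Baseline.** "After recruitment, information, such as the participant’s name, mobile phone number, and GA, was gathered during the baseline assessment".

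On masking, the randomisation section says that someone outside the trial's implementation did the allocation, that the implementing researcher was masked to it, and that interviewers were blind. Data Collection Procedures and Tools adds that data collectors and supervisors were not told the allocation. Of participants the article says: "It is not possible to blind participants due to the nature of the intervention". Midwives and health extension workers do not appear in any of these statements.

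**The concern.** Randomising kebeles balances kebeles. It does not balance the women chosen within them once the allocation exists. If the people who build the eligible list know the arm, the kind of woman who enters can differ by arm even though the kebeles were allocated at random.

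The screening leaves room for judgement. There is a 16-20 week window, sometimes dated by fundal height, and Eligibility Criteria for Clusters and Participants adds ability to read messages and plans to relocate. The mix of women also matters for the outcome. The Abstract says women enter whatever their antenatal care status, and Operational Definitions requires at least 8 ANC visits as one part of maternal health service usage. A shift between arms in the share of women already attending care would carry straight into that primary outcome.

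Strengths and Limitations presents cluster randomisation as the answer to poor comparability in earlier studies. The limitations it names are phone ownership and the lack of a cost-effectiveness assessment, not recruitment after allocation.

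**Working it through.** **1. Each step against the stated masking.** All of these steps follow allocation.

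| Step | Who acts | Stated to be masked? |
|---|---|---|
| Source list of pregnant women | Health extension workers' register | Not stated |
| Eligibility and gestational age | Midwives | Not stated |
| Random draw of 28 | Actor not stated | Chance decides, but only within the screened list |
| Explanation of the trial | Data collectors | Yes |
| Agreement to take part | The women | Time at which they learned their arm not stated |
| Baseline survey | Interviewers/data collectors | Yes |

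The open route is the first two rows. The random draw removes discretion over which eligible women are taken. It cannot undo a difference in who was judged eligible.

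**2. The plan's own sample size, to show whether order enters it.** Inputs from Sample Size for the ANC Visit: p1 = 0.2327, difference 0.15 (so p2 = 0.3827), Z = 2.24 and 0.84 (80% power), m = 28, ICC 0.003, autocorrelation 0.8, loss 4%.
- n = (0.2327×0.7673 + 0.3827×0.6173) × (2.24 + 0.84)² / 0.15² = 174.9, taken as 175.
- d_c = 1 + 27×0.003 = 1.081.
- r = 28×0.003×0.8 / 1.081 = 0.062. The formula is not legible in the text, so this form is assumed; it returns the stated r. Then d_r = 1 − r² = 0.996.
- 175 × 1.081 × 0.996 = 188.4 (stated 188); 188/0.96 = 195.8, so 196 per arm and 3 × 196 = 588 = 21 × 28.

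The plan's figures reproduce. The order of recruitment does not enter them, so there is no corrected sample size to give.

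**3. Which comparison is exposed.** Suppose selection shifts the outcome by b in both message arms. Message versus control is then off by b, while gain versus loss is off by b − b = 0. Gain versus loss is affected only if selection differs between the two message arms.

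**4. Purely illustrative scale.** The documents give no input for b. Assume that 10% to 20% of message-arm places go to women whose chance of the outcome is 30 to 40 points higher. Then b runs from 0.10×0.30 = 3 points to 0.20×0.40 = 8 points, against a target difference of 15. On the ANC sizing inputs, SE = √(2×0.2327×0.7673/188 × 1.081) = 0.0453. The chance of rejecting a true null is P(Z > 2.24 − b/SE) + P(Z < −2.24 − b/SE):
- b = 3 points: 5.9%
- b = 5 points: 12.8%
- b = 8 points: 31.8%

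The nominal rate is 2.5%. These rates follow from the assumed b and from the sizing proxy (more than 4 ANC visits, 23.27%). They do not describe the composite primary outcome and are not an estimate for this trial.

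**The case against.** The strongest reply is that order alone does not bias. Knowledge of the arm at recruitment does, and the article goes some way to exclude it.

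- **Consent and baseline.** The data collectors who explained the trial are said not to have known the allocation. The consent reads as one text for all eligible women, since control women too would have approved messages they were never sent. A filter that is the same in every arm does not bias the comparison. This stands, and it largely closes these two routes if the masking held.
- **Unblinded participants.** A reader might infer that women knew their arm when they agreed. The documents do not support that. The statement concerns the nature of the intervention, and no section says when women learned their arm. The one arm-specific action described, entry into the dispatch software, comes after baseline.
- **Midwives.** A reader might also infer that midwives knew the allocation. That is not stated either. This is a condensed article, and silence is not evidence of knowledge. It remains that the article has a section on who was masked, and the people who controlled entry are not in it.
- **Reporting already planned.** Multimedia Appendix 2 (not shown) gives participant flow, and Data Analysis Plan commits to CONSORT-EHEALTH. Part of the requested reporting may already exist.

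**Conclusion.** The point holds as a risk. Allocation came before listing, eligibility, dating, consent and baseline, and both relevant sections say so. The stated blinding and the random draw narrow the consent and baseline-survey routes. Screening and dating by midwives, and the register kept by health extension workers, are left without any stated masking. Differential selection between message and control kebeles is therefore possible.

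A reader might go further and conclude that the message-versus-control result is biased, or that the false-positive rate is 6% to 32%. The documents support neither. No arm imbalance is shown, and those rates rest on assumed shares and gaps applied to a proxy outcome. The size of any bias, and its direction, cannot be derived from the article.

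The conclusion assumes that the order was carried out as written. If midwives and health extension workers were in fact unaware of the allocation, little of the concern remains.

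**What to change.** **Design.** In all 21 kebeles, first complete the listing, eligibility and gestational-age assessment, the draw of 28, consent with one common information sheet, and the baseline survey. Only then generate and sort the random numbers that assign the arms. This needs no extra participants or staff. The downside is that arm-specific set-up of the messaging list starts after the baseline. It would have to fit between the March 2023 baseline and the May 2023 roll-out given in Results.

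**Now that enrolment is complete,** the order cannot be changed. The trial report should:
1. State whether midwives and health extension workers knew the allocation when women were listed and screened, and when women learned their arm.
2. Report by arm the numbers of women listed, eligible, approached, refusing and enrolled, in the participant flow if they are not already there.
3. Name possible recruitment bias as a limitation on the message-versus-control conclusions, next to the comparability claim in Strengths and Limitations.

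This costs some retrieval of screening records and a few sentences. If the counts were not kept by arm, the report should say so.

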### Randomization, Allocation Concealment, and Blinding

A total of 6 primary health care units, 2 from each district, were randomly selected, and kebeles in these primary health care units were used as units of randomization for the trial. A simple randomization with a 1:1 allocation was used to randomize the clusters (kebeles). After listing 30 kebeles that fulfilled the eligibility criteria, 21 of them were randomly selected for randomization. To assign the clusters to the intervention groups (gain-framed group, loss-framed group, and control group), the following steps were followed. First, the 21 clusters were alphabetically listed and labeled 1 to 21. Next, random numbers were generated using Excel 2019 (Microsoft Corp), and the generated values were copied and pasted as values next to the list of clusters. The list was then sorted in ascending order based on the generated random number. Finally, the first 7 clusters in the sorted list were assigned to the gain-framed group, the next 7 to the loss-framed group, and the last 7 to the control group. After the randomization, eligible pregnant women with a GA of 16-20 weeks were identified from the selected cluster by midwives. The midwives used 2 strategies: the LMP and the fundal height measurement technique in the case of an unknown LMP to determine the GA of mothers (Multimedia Appendix 2).

The allocation process was done by a person who was not involved in the implementation of the trial, and it was masked from the researcher involved in the implementation of the intervention. The interviewers who collected the data were blind to the intervention assignment. It is not possible to blind participants due to the nature of the intervention.

### Outcomes

The primary and secondary outcomes are provided in Textbox 1.

Primary and secondary outcomes.
**Primary outcomes**
Maternal health service usageNewborn care practice
**Secondary outcomes**
Knowledge about maternal health servicesKnowledge of danger signs (during pregnancy, labor and delivery, and the postnatal period)Knowledge of newborn care practiceKnowledge about newborn danger signsAttitude toward maternal health servicesAttitude toward newborn careSelf-efficacy toward maternal health service usageSelf-efficacy toward newborn care practiceIron supplementationMaternal morbidityNeonatal morbidity

### Operational Definitions

Operational definitions are as follows:

Maternal health service usage:when mothers receive at least 8 ANC follow-up visits, give birth in a health facility, and visit a health facility for PNC follow-up contact from health professionals within 7 days of delivery.Newborn care practice:this refers to the care provided to the baby from birth to 28 days of age by the mothers, including early initiation of breastfeeding, exclusive breastfeeding, feeding colostrum, thermal care, hygienic cord care, and seeking care for an ill newborn. If a mother feeds colostrum, initiates breastfeeding within 1 hour after birth, feeds a newborn only breast milk, practices thermal and hygienic cord care, and seeks care for her ill newborn, she is considered to be practicing newborn care, and if she misses one of them, she is considered to be not practicing newborn care.Knowledge about maternal health services:participants were asked to mention the recommended newborn care practice using 16 questions. All the responses were counted, and the higher score indicates a higher knowledge of newborn care practice.Knowledge of maternal danger signs:this was measured by 7 items related to maternal danger signs during pregnancy, labor & delivery, and the postnatal period such that yes=1 for correct statements and no=0 for incorrect statements. The scores of correct answers were summed, and a higher score was interpreted as a higher level of knowledge of maternal danger signs.Knowledge of newborn danger signs:this was measured by 12 items related to neonatal danger signs, such that yes=1 for correct statements and no=0 for incorrect statements. The scores of correct answers were summed, and a higher score was interpreted as a higher level of knowledge of newborn danger signs.Knowledge of newborn care practice:participants were asked to mention the recommended newborn care practice using 7 questions. All the responses were counted, and the higher score indicates a higher knowledge of newborn care practice.Attitude toward maternal health services:this refers to mothers’ feelings toward maternal care practice. Attitude toward maternal care practice was measured by 10 items on a 5-point Likert scale ranging from 1=strongly disagree to 5=strongly agree. The cumulative scores were used in the analysis once negatively phrased items were reverse-coded. A higher composite score indicated a more favorable attitude toward maternal care practice.Attitude toward newborn care practice:this refers to mothers’ feelings toward newborn care practices. It was measured by 16 items, which are designed in a 5-point Likert scale format ranging from 1=strongly disagree to 5=strongly agree. The sum score was used in the analysis after reverse coding the negatively worded items. The higher composite score was interpreted as a favorable attitude toward newborn care practice.Self-efficacy to practice maternal health service usage:self-efficacy in practicing maternal care is an individual belief in mothers’ ability to perform maternal care practices. It was measured by 10 items designed on a 5-point Likert scale ranging from 1=strongly disagree to 5=strongly agree. Once negatively worded items were reverse-coded, the sum score was used in the analysis. A score with a high value indicated greater self-efficacy in practicing maternal care.Self-efficacy to practice maternal and newborn care:this refers to an individual belief in one’s ability to perform maternal and newborn care practice. It was measured by 9 items, which are designed in a 5-point Likert scale format ranging from 1=strongly disagree to 5=strongly agree. The sum score was used in the analysis after reverse coding the negatively worded items. A score with a high value indicates higher self-efficacy toward practicing newborn care.

### Data Collection Procedures and Tools

The baseline survey was conducted in March 2023, while the end-line survey was conducted in February, 2024. Trained interviewers collected data for both the baseline and end-line surveys through face-to-face interviews using a structured questionnaire. The questionnaire addressed various domains, including sociodemographic factors, socioeconomic factors, obstetric history, maternal health service usage, newborn care practice, knowledge about maternal health services, knowledge about maternal danger signs, knowledge about newborn danger signs, knowledge about newborn care practices, attitude toward maternal health services, attitude toward newborn care practice, self-efficacy toward maternal health services, self-efficacy toward newborn care practice, iron supplementation, and maternal and neonatal morbidity. Participants who were lost to follow-up were recorded, along with their reasons for discontinuation and the outcome of their pregnancy. The data were checked for inconsistencies and errors during the data collection period by dedicated supervisors and submitted to the central data management unit.

A total of 10 data collectors and 2 supervisors were recruited during each data collection period. A 2-day training was given for data collectors and supervisors on the questionnaire content, measurements, ethical issues, and how to use the ODK app (during end-line assessment), and they were kept uninformed about cluster allocation.

### Data Management

The collected data during the baseline and end-line was checked for completeness at the time of data collection by supervisors, and questionnaires with missing items were communicated with data collectors for correction. Double entry was done for baseline data to identify and manage mistakes during the data entry, while the end-line data were retrieved from KoBo Toolbox. Data cleaning was done to identify the duplicate records and missing and outlier values; to verify that the values were in the proper format and expected range; and to correct the errors. Only the study team has access to the intervention data sets. Information about clusters and participants was not shared with any third party, both during and after the intervention. Moreover, all personal identifiers were removed from the database, and paper-based filled questionnaires were stored in a locked cabinet. Data were stored in a database on a password-protected computer, and only the research team could access it.

### Data Analysis Plan

Double-data entry was accomplished using Epi-data (version 4.6, released in 2020; the EpiData Association) and exported to the SPSS (version 25; IBM Corp) for analysis. The report of this study will be made according to the CONSORT-EHEALTH (Consolidated Standards of Reporting Trials of Electronic and Mobile HEalth Applications and onLine TeleHealth) standards for reporting randomized controlled trials. Exploratory subgroup analysis was done to identify whether the effects of intervention vary with sociodemographic characteristics, socioeconomic characteristics, obstetric history, and psychological factors. To assess the characteristics of the study population through the lenses of different variables, selected data were tabulated by study arms; this helped us to identify variations and similarities among study arms. The summary statistics used for categorical variables were frequencies and percentages. For continuous variables, the mean and standard deviation will be presented.

To observe the effectiveness of mobile phone messaging-based message framing interventions for improving maternal and newborn health service usage, we will use an intention-to-treat approach where all randomized participants will be included in the statistical analysis, regardless of whether they received the intervention or not. A generalized linear mixed model will be used to adjust for both the clustering effect and the participant-level intracluster correction. The outcome variables are assumed to have a multivariable normal distribution. The odds ratio will be used to measure the effectiveness of the intervention on the outcome variable with a 95% CI.

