**Methods:**

A 3-arm cluster-randomized trial design was used to evaluate the effects of mobile phone–based intervention on maternal and newborn health service usage. The trial arms were (1) gain-framed messages (2) loss-framed messages, and (3) usual care. A total of 21 health posts were randomized, and 588 pregnant women who had a gestational age of 16-20 weeks, irrespective of their antenatal care status, were randomly assigned to the trial arms. The intervention consisted of a series of messages dispatched from the date of enrolment until 6-8 months. The control group received existing care without messages. The primary outcomes were maternal health service usage and newborn care practice, while knowledge, attitude, self-efficacy, iron supplementation, and neonatal and maternal morbidity were secondary outcomes. The outcomes will be analyzed using a generalized linear mixed model and the findings will be reported according to the CONSORT-EHEALTH (Consolidated Standards of Reporting Trials of Electronic and Mobile HEalth Applications and onLine TeleHealth) statement for randomized controlled trials.

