## Results

The recruitment of 588 intervention participants and the baseline survey were carried out in March 2023. The intervention was rolled out starting in May 2023 and ending in December 2023. The end-line assessments were conducted in February 2024. We are working on data management, and we expect the analysis to be completed by May 30, 2024. The publication of the results is anticipated in August, 2024.

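### The primary outcome counts antenatal visits made before exposure, the start of exposure is stated two ways, and the stated model names no baseline covariate

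*Protocol article*

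**What the plan says.** **Outcome.** Under Operational Definitions, maternal health service usage is met "when mothers receive at least 8 ANC follow-up visits, give birth in a health facility, and visit a health facility for PNC follow-up contact", the last within 7 days of birth. No start date for counting visits is given. The Abstract (Methods) says the trial took "588 pregnant women who had a gestational age of 16-20 weeks, irrespective of their antenatal care status".

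**Start of exposure.** The Abstract (Methods) says: "The intervention consisted of a series of messages dispatched from the date of enrolment until 6-8 months". The descriptions of the gain-framed and loss-framed arms agree with this. The Results section puts recruitment and the baseline survey in March 2023 and then says: "The intervention was rolled out starting in May 2023 and ending in December 2023". The Abstract (Results) gives the same dates.

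**Model.** The Data Analysis Plan says: "A generalized linear mixed model will be used to adjust for both the clustering effect and the participant-level intracluster correction". It names no baseline value and no district term.

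**What is available.** Data Collection Procedures and Tools lists one set of questionnaire domains for both surveys, "including sociodemographic factors, socioeconomic factors, obstetric history, maternal health service usage, newborn care practice" among them, together with the knowledge, attitude and self-efficacy scores. The Recruitment section says gestational age was recorded at baseline.

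**Design.** Simple, unstratified randomisation assigned 21 kebeles from three districts, 7 to each arm. Sample Size Determination multiplies by a repeated-assessment factor d_r, given as 0.996 (ANC) and 0.953 (newborn care).

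**The concern.** Part of the 8-visit count is settled before any message can act, so visit history at entry is likely to be prognostic for the primary outcome. With 7 clusters per arm and no stratification, the arms can differ by chance in such history, and a model without baseline terms leaves that difference in the estimate and in its standard error.

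The sample size also takes a reduction that belongs to an analysis using the baseline assessment, while the stated model does not say that the baseline is used.

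The two accounts of when messages began affect interpretation. If messages began at enrolment, a null result says that messages through the second half of pregnancy did not raise attendance to the target. If they began in May, it may say only that they came too late for many women to reach 8 visits.

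**Working it through.** **1. The plan's own ANC figure.** Inputs from Sample Size Determination: control 23.27%, effect 15 points, two-sided alpha 0.025 (Z = 2.24), power 80%, m = 28, ICC 0.003, autocorrelation 0.8, loss 4%.

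- n = (2.24 + 0.84)² × (0.2327×0.7673 + 0.3827×0.6173) / 0.15² = 175.2 (unrounded Z values)
- d_c = 1 + 27×0.003 = 1.081
- r = 28×0.003×0.8 / 1.081 = 0.062; d_r = 1 − r² = 0.996
- n × d_c × d_r = 188.7 (stated 188); 188/0.96 = 195.8, so 196 per arm and 588 in total

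The figures reproduce. The formula for r is not shown in the text, but this form returns the stated 0.062.

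**2. What the baseline credit is worth.** Leave out d_r.

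- ANC: 175.2 × 1.081 = 189.4 instead of 188.7, or 0.4%.
- Newborn care (74.8%, ICC 0.013): n = 118.3, d_c = 1.351, r = 28×0.013×0.8 / 1.351 = 0.2155, d_r = 0.9535. This gives 152.4 (stated 152) with the credit and 159.9 without, about 5%. The stated r of 0.251 would give d_r = 1 − 0.251² = 0.937, not the stated 0.953; 0.2155 fits.
- Without the credit, newborn care needs 159.9/0.96 = 166.6, so 167 per arm and 501 in total, still below 588.

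The credit is a cluster-level one and hardly moves the trial size. It matters because it shows that the sizing presumes use of the baseline.

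**3. Gestational age at a May start.** Enrolment 1-31 March at 16w0d to 20w6d.

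| Case | Days to 1 May | Weeks on 1 May |
|---|---|---|
| 16w0d on 31 March | 31 (4.4 weeks) | 20.4 |
| 20w6d on 1 March | 61 (8.7 weeks) | 29.6 |

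For the second woman a first message on 31 May would come at 33.9 weeks (91 days). With birth assumed at 40 weeks, a 1 May start leaves 10.4 to 19.6 weeks, in which a woman with no earlier visits would need all 8.

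**4. Individual-level gain (assumed).** The documents give no correlation between baseline covariates and outcome. With 196 per arm, 4% loss and d_c = 1.081, the effective n is 196×0.96/1.081 = 174 per arm. Power by a pooled-variance normal approximation is 78.8% with no baseline term and 79.0% with d_r. If covariates correlate R with the outcome, residual variance falls by the factor 1 − R²:

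| Assumed R | Variance factor | Power |
|---|---|---|
| 0.2 | 0.96 | 80.6% |
| 0.3 | 0.91 | 82.9% |
| 0.4 | 0.84 | 86.0% |
| 0.5 | 0.75 | 89.9% |

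This is linear-model reasoning. It carries over only loosely to an odds ratio, and the control rate used is for more than 4 visits, not 8.

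**5. Chance imbalance.**

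- Districts: the split of the 21 kebeles is not stated. Assuming 7 per district, 200,000 random allocations give a 14% chance that some arm has 5 or more clusters from one district, 22% that some arm has none from one, and 35% that the gain and control arms differ by 3 or more in some district.
- A yes/no baseline factor, prevalence 30-50% (assumed), ICC 0.003-0.013: SE = √[2p(1−p)(1+27×ICC)/196] = 0.048 to 0.059, so a 95% range of about ±9 to ±12 points between arms. How far this reaches the outcome depends on the unknown association.
- Between-cluster variation in the ANC outcome at ICC 0.003: SD = √(0.003×0.2327×0.7673) = 2.3 points. Over 7 versus 7 clusters, 1.96 × 2.3 × √(2/7) = 2.4 points, against a 15-point target.

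**The case against.** The strongest reply is that the Data Analysis Plan is silent on covariates and does not exclude them, and that a condensed article may leave the list to an analysis plan. The participant-level term could also mean repeated measures on women, which would bring baseline rows into the model. Both stand. A reader might infer that the plan adjusts for clustering only and discards the baseline; the text does not say so. It remains that the article states the sample-size credit and the collected variables, but no use of them in the model.

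A reader might also infer that the unadjusted analysis is biased. It is not: randomisation balances earlier visits in expectation, and chance imbalance is within the nominal error rate. Counting total contacts is also a legitimate endpoint, in line with the 8 contacts cited for usual care.

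Three further points stand:

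- A count of current-pregnancy ANC visits at baseline is likely but not documented. The shared domain list includes newborn care practice, which has no index-pregnancy value at 16-20 weeks.
- At the plan's ANC ICC, between-cluster imbalance is worth only about 2.4 points, which weakens the case for district as a primary-model term with 21 clusters.
- Visits after the first message cannot be defined in a control arm that receives none.

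The reply does not remove the start-date conflict, which lies between passages of this article.

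**Conclusion.** The point holds as an avoidable loss of precision and of protection against chance imbalance, joined to an unresolved contradiction about when exposure began. It is not an error that invalidates the comparison.

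Two things follow from the documents alone: visits before enrolment count toward the primary outcome, and the passages disagree on the start of messages. A 1 May start would mean about 20 to 30 weeks of gestation.

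The size of the loss is not fixed by the documents. Their own credit is worth about 0.4% (ANC) and 5% (newborn care). A gain of several power points needs individual covariates with an assumed R of 0.3 or more, and the district probabilities assume 7 kebeles per district. Validity in expectation also assumes that enrolment of women, which followed cluster allocation, was not selective by arm.

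The change is worth making because it is nearly free and because the start date governs how a null result is read.

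**What to change.** (a) Prespecify a short list of fixed effects in the primary model: gestational age at enrolment, parity or obstetric history, and baseline ANC use where the baseline survey recorded it for the current pregnancy. Adjust each knowledge, attitude and self-efficacy score for its baseline value. Show the unadjusted model, and a model adding district, as sensitivity analyses. State what the participant-level term represents. Choose the covariates for expected prognostic value, not from the tabulation by arm that the Data Analysis Plan describes.

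(b) Reconcile the passages on when messages started, and report gestational age at that date.

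(c) If visit timing was recorded, report ANC visits after a common reference date applied to all three arms (enrolment, or the rollout date) as a supportive outcome.

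The cost is wording in the analysis plan, a few degrees of freedom, and an odds ratio that is conditional on the covariates and so not directly comparable with the unadjusted one. Gestational age, obstetric history and the baseline scores are already collected. Whether current-pregnancy ANC use and visit dates were recorded has to be confirmed first.
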